## Abstract

**Background:**

Low-dose aspirin (LDA) has been proposed as a safe and inexpensive prophylactic agent. Studies in European/Western populations have shown promising results indicating that LDA can reduce the occurrence of pre-eclampsia (PE) in women with identifiable risk factors. However, few controlled trials, particularly large randomized controlled trials, have been performed in Asian populations. The aim of this project is to evaluate the effect of LDA for PE prevention on high-risk pregnant women in China, where PE is highly prevalent and the LDA supply status is commonly suboptimal.

**Methods/design:**

An open-label, multicentre randomized controlled trial is being conducted at 13 tertiary hospitals in 11 provinces in China. A total of 1000 eligible women with high-risk factors for developing PE according to their medical histories are being randomized into two groups: a control group (*n* = 500) and an intervention group (*n* = 500). Women with high-risk factors, such as a history of PE, chronic hypertension, type 1 or 2 diabetes, advanced maternal age, obesity, family history of PE or nulliparity are eligible. The control group is advised to undergo routine examinations, whereas the intervention group undergoes the routine examinations and receives LDA. LDA (100 mg/d) should be prescribed at night, initiating from early pregnancy (12–20 weeks of gestation) and lasting until 34 weeks of gestation. Demographic data and clinical endpoint outcomes, as well as biological samples (e.g., maternal blood, cord blood, amniotic fluid and placental samples), will be collected. The primary outcome is the occurrence of PE, and the secondary outcomes include maternal and neonatal outcomes and maternal biomarker levels.

**Discussion:**

This is the first and largest multicentre randomized controlled trial to assess the effect of LDA in preventing PE in a Chinese population. The results will potentially influence the prenatal care recommendations in China regarding intervention with LDA for PE.

**Trial registration:**

ClinicalTrials.gov, NCT02797249. Registered on 7 June 2016.

**Electronic supplementary material:**

The online version of this article (10.1186/s13063-018-2970-3) contains supplementary material, which is available to authorized users.

## Background

Pre-eclampsia (PE) affects approximately 3–5% of pregnant women [1], and this prevalence varies from country to country. It has been reported that the prevalence of PE is 4% in low- and middle-income countries [2] and 2.8% in China [3]. Although its prevalence is low, PE can cause substantial maternal and perinatal morbidity and mortality [4]. When left untreated, severe complications of PE, such as eclampsia, stroke, pulmonary oedema or kidney failure, can develop, and they can all be fatal [5]. Moreover, PE is also associated with preterm birth, foetal growth restriction and babies who are small for gestational age (SGA) [1]. Once PE develops, the only effective treatment is prompt delivery, with serious neonatal harm when far from term (< 34 weeks of gestation) [6]. Therefore, it is necessary to determine an effective early identification strategy and undertake a preventive measure for women at high risk of PE in order to reduce the prevalence of the complication.

For the early prevention of PE, the most consistent and promising prophylactic agent appears to be low-dose aspirin (LDA) [6]. Aspirin has become one of the most commonly used drugs, given its role as an analgesic, antipyretic and cardiovascular prophylactic agent. Studies have shown that aspirin can decrease the occurrence of pregnancy disorders, including PE [7], preterm birth and foetal growth restriction [8], on the basis of its anti-inflammatory and anti-thrombotic effects. One of the mechanisms by which aspirin exerts its beneficial effect is the selective inhibition of thromboxane synthesis without affecting prostacyclin synthesis, thus restoring a balance between thromboxane and prostacyclin [9, 10]. Besides, aspirin seems to improve defective trophoblast syncytialization by altering the production of specific cytokines, decreasing apoptosis and altering cell aggregation and fusion [11]. Moreover, in hypoxic conditions, aspirin can inhibit the expression of soluble fms-like tyrosine kinase 1 (sFlt1) in human trophoblasts and thus shows pro-angiogenic activity [12].

In most previous studies, the recommended dose of aspirin for PE prevention has been 60 to 150 mg/d, and 100 mg/d is used most commonly [13]. Studies recommend the initial use of aspirin after 12 weeks of gestation, and there is no research on aspirin treatment before 12 weeks of gestation [6]. Previous studies also have shown that the prevention of PE and foetal growth restriction using aspirin has a dose-response effect, and thus LDA is recommended to be initiated before 16 weeks of gestation [14]. Regarding drug safety, aspirin appears not to increase the rate of placental abruption, postpartum haemorrhage or foetal intracranial haemorrhage [6].

The prophylactic use of LDA for PE was first reported in 1978 [15], and since then numerous studies have reported the potential value of LDA in PE prevention among high-risk pregnant women. Authors of a Cochrane meta-analysis published in 2004 reported that the administration of antiplatelet agents in high-risk women could reduce the rate of PE by 19% [16]. The World Health Organization and several countries, including the United States, the United Kingdom, Canada and Australia, also recommended in their guidelines the use of LDA for the prevention of PE in high-risk pregnant women [17–21].

However, regarding the details of aspirin as a preventive treatment for PE, guidelines differ considerably from country to country. In addition, most randomized controlled trials (RCTs) have focused on Caucasian or black individuals; data for Asian populations are lacking [22]. Besides, only a few small-sample studies in China have been reported [23, 24]. There is scant evidence from large RCTs to guide the use of LDA for PE prevention for Chinese pregnant women. Therefore, we decided to conduct a large-population RCT in China to evaluate the role of LDA prophylactic treatment for PE prevention to fill this important gap in the literature and to ultimately translate research into practice by providing policy recommendations.

## Methods/design

### Study design

The low-dose Aspirin in the Prevention of Pre-eclampsia in China (APPEC) study is designed as multicentre, open-label RCT research. This study is being conducted at 13 tertiary hospitals in 11 provinces in China: Beijing, Henan, Guangdong, Shanghai, Jiangsu, Shandong, Hunan, Gansu, Shan-xi, Shanxi and Chongqing. A total of 1000 eligible women will be recruited and randomized into the control group or the intervention group, with an allocation ratio of 1:1. The start of the recruitment was in December 2016, and we anticipate that the study will be completed in approximately 3 years.

### Objective

The aim of this study is to evaluate the effect of LDA administered from early pregnancy in Chinese pregnant women with high-risk factors. The following hypothesis will be tested: The administration of LDA to pregnant women from early pregnancy (12 to 20 weeks of gestation) will reduce the occurrence of PE by 20%. Moreover, clinical information and maternal biological samples will also be collected for further mechanistic research.

### Participants

Participants will be eligible for registration in this study if they meet all of the inclusion criteria and none of the exclusion criteria, listed below.

#### Inclusion criteria

Aged ≥ 18 and < 55 yearsSingleton pregnancyLive foetus at gestational age 12–20 weeksBe at high risk of developing PE based on clinical risk factors such as the following:a. At least one high-risk factor, namely history of PE, diabetes mellitus (type 1 or 2) or chronic hypertensionb. At least two intermediate-risk factors, including obesity (≥28 kg/m^2^), advanced maternal age (≥ 35 years), family history of PE (mother and/or sister) or nulliparityFit to undergo all procedures listed in the protocolAble to provide written informed consent

#### Exclusion criteria

Allergic to aspirinAsthmaPeptic ulcersSevere heart, liver or renal disease in which the patient cannot tolerate the treatmentRheumatic immune diseaseMental diseaseAlcohol or drug abuseIn vitro fertilizationPrevious registration in another drug trial within the previous 3 monthsDifficulty in undergoing any procedure listed in the protocol

### Randomization

Randomization will be performed using a web-based computerized central randomization system, the Interactive Web Response System (http://bjdx.clinicalcloud.com.cn/Login.aspx), in a 1:1 allocation ratio. The website randomly assigns a randomization code to each participant. Eligible women will be randomized to one of the two groups. Knowledge of the treatment allocation is open to the investigators and the participants.

### Sample size calculation

For the primary outcome indicator, “pre-eclampsia,” we assume that the estimated detection rate for PE is 20% in the control group, according to previous studies [25–27]. The occurrence of PE in the intervention group is supposed to be 16%, and thus the estimate of risk reduction with the intervention is 20%. For 80% power and a level of significance set at 0.05, 446 participants are required in each group. Thus, the total number of women required in the study is 892. Accounting for 10% withdrawal/loss to follow-up, 981 women will need to be recruited. Finally, we set the number of women to be recruited into the study at 1000 (500 per group). The power calculation was performed using PASS 2011 software (NCSS, Kaysville, UT, USA).

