### Statistical analysis

Baseline characteristics will be calculated using Student’s *t* test, the chi-square test or Fisher’s exact test as appropriate for comparisons across groups. Data will be analysed on an intention-to-treat basis to compare primary and secondary outcomes in both groups. The primary analysis will be done with generalized estimating equation regression models of the occurrence of PE, with adjustment for the effect of the risk factors for PE at screening and the study sites. The OR with 95% CI will be calculated to quantify the treatment effect. Moreover, exploratory subgroup analysis will be performed to identify whether the effects of intervention vary with the risk factors for PE, including chronic hypertension, pre-existing diabetes, history of PE, obesity, advanced age, nulliparity and family history of PE. The initial intervention weeks of gestation (e.g., < 16 weeks vs. ≥16 weeks of gestation) and its interaction with aspirin preventive treatment will also be investigated. A *P* value < 0.05 will be considered statistically significant. Statistical analysis will be performed by a statistician using IBM SPSS Statistics version 22.0 (IBM, Armonk, NY, USA) and Stata version 11.0 (StataCorp, College Station, TX, USA) software.

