In conclusion, our study is novel in its assessment of the effect of LDA for PE prevention in a large Chinese population, which will be helpful in guiding healthcare providers regarding whether they should recommend LDA as a preventive drug to patients in China. Because there is no clear evidence that such agent is any more or less effective in reducing the relative risk for any particular subgroup, further research is needed to focus on the evaluation of LDA’s preventive effect in women with a single risk factor, such as nulliparity, chronic kidney disease, obesity and so forth. Besides, a recent study showed that aspirin’s effects on cardiovascular and oncological diseases varies with different body sizes and that a one-dose-fits-all approach to aspirin is unlikely to be optimal [30]. It is unknown whether the preventive effect of aspirin on pregnant women varies with their different body sizes. Therefore, this information should also be discussed with women at risk of PE to help them to choose a suitable dose of aspirin for PE prevention. Overall, this study will provide information for preventive treatment with aspirin in Chinese pregnant women, especially for populations with a high risk of PE.

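### 446 women per group give about 34% power, not 80%, for 20% versus 16% pre-eclampsia; 80% power needs about 1,447 per group

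*Protocol article*

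**What the plan says.** The Sample size calculation section gives every input that is needed. For controls, "we assume that the estimated detection rate for PE is 20% in the control group". For the aspirin group, "The occurrence of PE in the intervention group is supposed to be 16%, and thus the estimate of risk reduction with the intervention is 20"%. It then states: "For 80% power and a level of significance set at 0.05, 446 participants are required in each group". The total follows: "Thus, the total number of women required in the study is 892". An allowance of 10% for withdrawal and loss brings this to 981, rounded to a target of 1,000, or 500 per group.

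The effect size agrees with the rest of the article. The Objective section hypothesises that aspirin "will reduce the occurrence of PE by 20"%, which is 20% falling to 16%. Study design fixes randomisation "with an allocation ratio of 1:1". Whether the sample size is one- or two-sided is not stated. The Statistical analysis section says only "A *P* value < 0.05 will be considered statistically significant" and plans an odds ratio with a 95% confidence interval, which points to two-sided testing.

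**The concern.** A four-point difference around a rate of 18% is small, and a few hundred women per group is well short of what such a difference normally requires. If 446 is wrong, so are 892, 981 and 1,000, because each is derived from it.

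At stake is how the primary result will be read. A trial described as having 80% power for a 20% reduction invites the reader to treat a non-significant result as fair evidence against an effect of that size. The Discussion expects the findings to be "helpful in guiding healthcare providers regarding whether they should recommend LDA as a preventive drug to patients in China". If the real power is far lower, a null result is the likely outcome even when the hypothesis is true, and it says little about whether aspirin works.

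**Working it through.** **Inputs.** Control rate p1 = 0.20, aspirin rate p2 = 0.16, significance level 0.05 and power 80% (Sample size calculation); 1:1 allocation (Study design). Two-sided testing is assumed, and one-sided is tried as well. The mean rate is 0.18 and the difference is 0.04.

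**Step 1: try to reproduce 446.** The pooled-variance formula is

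n = [z(α)·√(2·p̄·(1−p̄)) + z(β)·√(p1(1−p1) + p2(1−p2))]² / (p1−p2)²

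= [1.96·√(2·0.18·0.82) + 0.8416·√(0.16 + 0.1344)]² / 0.04²

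= [1.0649 + 0.4567]² / 0.0016 = 1,446.9, so **1,447 per group**.

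Other standard methods do not approach 446:

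| Method | Two-sided n per group | One-sided n per group |
|---|---|---|
| Pooled variance | 1,447 | 1,140 |
| Continuity-corrected | 1,497 | 1,190 |
| Unpooled variance | 1,445 | 1,138 |
| Arcsine | 1,445 | 1,138 |
| Log odds ratio | 1,454 | 1,145 |
| Log relative risk | 1,459 | 1,149 |

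A one-sample formula, which would not fit this design, gives 552 to 747. The stated figure is not reproduced: 1,447 / 446 = 3.2.

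**Step 2: power at the planned size.** Power ≈ Φ{[0.04·√n − 1.0649] / 0.5426} for the two-sided test.

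- n = 446: [0.8447 − 1.0649] / 0.5426 = −0.406, power about 34%.
- n = 450 (500 less 10%): [0.8485 − 1.0649] / 0.5426 = −0.399, power 34.5%.
- n = 500 (no loss): [0.8944 − 1.0649] / 0.5426 = −0.314, power 37.7%.

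Exact binomial enumeration of the chi-square test gives 34.3%, 34.6% and 37.6%. One-sided power is 46.4% at 446 and 50.1% at 500. Even if 892 or 1,000 were read as the size of each group, two-sided power would be only 59% or 64%.

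**Step 3: what 446 per group can detect.** Holding the control rate at 20% and solving for the aspirin rate at 80% two-sided power:

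- 446 per group: 13.0%, a relative reduction of 35%.
- 450 per group: 13.1%, also 35%.
- 500 per group: 13.4%, a reduction of 33%.

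The Background section cites a meta-analysis with a 19% reduction, close to the hypothesised 20% and well below 33 to 35%.

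**Step 4: what the hypothesised result would look like.** Take 450 women per group and exactly 20% versus 16%, that is 90 and 72 cases. RR = 0.80; SE of log RR = √(0.80/90 + 0.84/72) = 0.143; 95% CI 0.60 to 1.06. On the planned odds ratio scale (unadjusted), OR = (72·360)/(378·90) = 0.76; SE of log OR = √(1/72 + 1/378 + 1/90 + 1/360) = 0.174; 95% CI 0.54 to 1.07. Neither is significant. With 20% in controls, the observed aspirin rate would have to be about 15.0% or lower (RR about 0.75).

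**Step 5: the allowance for loss.** 892 × 1.1 = 981, as stated. Dividing by 0.9 would give 992. The target of 1,000 covers both, so this is harmless. Applied to the correct size, 2 × 1,447 = 2,894, and 2,894 / 0.9 gives 3,216 women.

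**The case against.** Several defences deserve a hearing.

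- **Misread digit in the text.** This fails: 892 is twice 446 and 981 is 892 × 1.1, so the article carries 446 through consistently.
- **Unstated sidedness, or an unseen full protocol or analysis plan.** A one-sided test needs 1,140 per group and reaches only 46 to 50% power. The article itself states both rates, the level, the power and the result. This is a contradiction among stated figures, and no further document can make 446 follow from them.
- **Covariate adjustment.** The primary model adjusts for risk factors and site, so the unadjusted power above is not exactly the power of the planned analysis. That is fair. But the sample size paragraph claims no such gain, and adjustment would have to remove about 69% of the variance (1 − 446/1,447) to close the gap, which is not plausible.
- **The true effect may be larger.** Also fair: at about 20% versus 13%, power is near 80%. The expectation of a missed effect is conditional on the article's own hypothesis being exactly right.
- **No one says a null result will be reported as no effect.** Correct. The analysis section plans an interval estimate, so misreading is a risk and not a stated intention. A rule for interpreting a null result is therefore a useful addition, but it does not follow from the arithmetic.

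The origin of 446 cannot be settled from the article. It resembles the computed 1,446.9 with its first digit dropped, and it is also near the 441 per group needed for 20% versus 13%. Nothing here depends on which, if either, is the explanation.

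**Conclusion.** The concern holds. The requirement for the stated inputs is about 1,447 women per group; 446 is less than a third of that. The planned 1,000 women give about 35% two-sided power after 10% loss and about 38% with none, against the 80% claimed. If the truth is 20% versus 16%, roughly two trials in three of this size would be non-significant. The conclusion rests on the article's own rates and on a simple comparison of two proportions. It does not depend on sidedness or on the choice of formula, and covariate adjustment could not plausibly overturn it. Because the false figure is the central design claim for the primary outcome, it must be corrected.

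**What to change.** In the Sample size calculation section, delete the claim that 446 per group gives 80% power for a 20% reduction. State instead that 1,000 women, about 900 evaluable, give about 35% two-sided power (38% with no loss) for 20% versus 16%, and 80% power only for about 20% versus 13%. State the sidedness of the test. If a different effect size was intended, it should be given and squared with the 16% in that section and the 20% reduction in the Objective.

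It would also help to add to the Statistical analysis section that a non-significant primary result will be read from its confidence interval, and will not be presented as evidence that aspirin is ineffective while that interval still includes the hypothesised effect. Since the planned measure is an odds ratio, the reference value should be on that scale: 20% versus 16% is an odds ratio of (0.16/0.84)/(0.20/0.80) = 0.76 before adjustment.

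The cost is a rewording and a less favourable power statement. No extra women are needed. Keeping the 80% claim for a 20% reduction would instead mean recruiting about 3,216 women, more than three times the present target.

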### Recruitment and trial procedure

Participants will be identified for their first antenatal care (before 20 weeks of gestation) in our study sites. The enrolment of patients will be at the obstetrics clinic, and a brief assessment card has been designed to determine the eligible women. Recruitment strategies are dependent on the local hospitals, including recruitment advertisement, online news, advertisements in training classes for pregnant women, and doctor screening. Our study sites can determine the most effective method for their hospitals.

Pregnancy is confirmed via transabdominal B-mode ultrasound. Then the investigators will evaluate the risk factors and baseline conditions of pregnant women, and those who meet the eligibility criteria will be enrolled in the study. Trial information will be provided verbally and with a written information sheet. Eligible women will be encouraged to take time to consider involvement in the study and to discuss the participation with their partners and/or family prior to providing written consent. All eligible women will provide written informed consent and receive written information about the trial drug. In addition, participants will be randomized and assigned with a randomization code, which will determine who receives 100 mg of aspirin daily and who does not. Details of antenatal and postpartum care are outlined in Figs. 1 and 2 and Additional file 1, which present the study flow chart; the Standard Protocol Items: Recommendations for Interventional Trials (SPIRIT) schedule of enrolment, interventions and assessments; and the SPIRIT checklist, respectively [28]. All of the participants will be free to withdraw from the study at any time if they wish, and appropriate on-going antenatal care will be arranged for the pregnant women according to their clinical risks.

**Fig. 1 Fig1:**
[figure not shown]
Flow chart of participants in the screening study and the randomized controlled trial

**Fig. 2 Fig2:**
[figure not shown]
Standard Protocol Items: Recommendations for Interventional Trials (SPIRIT) figure. Schedule of enrolment, interventions and assessments for the APPEC (low-dose Aspirin in the Prevention of Pre-Eclampsia in China) study

### Intervention and control groups

Women will be assigned into one of two groups. The control group will receive standard antenatal care for high-risk women, whereas the intervention group will receive standard antenatal care for high-risk women plus aspirin prophylactic treatment. LDA (100 mg/d, enteric-coated aspirin tablets; Bayer Corporation, Leverkusen, Germany) should be taken nightly from the recruitment time (at 12–20 weeks of gestation) and stopped at 34 weeks of gestation or in the event of early delivery. This is an open-label RCT, and all of the participants, clinicians and investigators will be aware of the study group assignment.

### Specimen collection

Blood samples will be routinely collected at each visit. These samples will be stored and will be measured only after delivery. Cord blood and placental samples will be collected at delivery. Biomarkers (such as sFlt1, soluble endoglin [sEng] and placental growth factor [PlGF]) and further mechanistic research on PE and the effect of aspirin prevention will be performed. These results will not be made available to the managing clinicians and will not affect management.

